### Secondary outcome measures

#### Compliance

Compliance, i.e. to what degree the participants are able to sustain the exercise regimen three months after participating in the project, will be one secondary outcome measure.

#### Change in blood pressure

Blood pressure will be measured as a secondary outcome, reflecting physiological stress response and cardiovascular health. As the link between blood pressure and anxiety remains underexplored, this study may provide novel insights into this relationship.

Participants’ changes in blood pressure, i.e. any difference between blood pressure measured at inclusion and at the end of the 4-week intervention, will be a secondary outcome measure.

Blood pressure at baseline is also part of the medical screening to exclude participants with very high blood pressure not compatible with exercise participation.

#### Heart rate variability

Heart rate variability (HRV), derived from ECG recordings, will be applied as a physiological indicator of autonomic regulation and stress response. HRV provides an objective complement to the self-reported anxiety measures (HADS and BAI), which measure the participants’ subjective experience of anxiety symptoms.

#### Adherence

Adherence will be assessed by the number of completed sessions and heart-rate data compliance. The training schedule is flexible, allowing participants to make up missed sessions in subsequent weeks to support adherence.

## Sample size calculation

The sample size calculation of the present study was informed by data from a previous study [21] on psychological effects of high-intensity exercise, which showed a significant reduction in anxiety levels in 33 participants with anxiety disorders. We conducted a power calculation using https://clincalc.com/stats/samplesize.aspx. We assumed a baseline mean of 30 on the Beck Anxiety Inventory (BAI) for each group. The expected post-treatment BAI scores are 14 for the high-intensity group and 22 for the low-intensity group. With a significance level (alpha) of 0.05, SD of 7 and 80% power, the required sample size is 24. This means we need 12 participants per group to detect significant differences using a two-tailed *t*-test. Previous studies have found that the average attrition rate is 20% [33].

To account for an expected attrition rate of about 20% [33], the final target sample size is 30 participants (15 per group), representing the minimum required for adequate power. Additional participants may be included if recruitment permits, to further strengthen statistical power. Potential missing data will be addressed using linear mixed-model analyses, since this analysis is robust to missing-at-random mechanisms. Sensitivity analyses based on both intention-to-treat and per-protocol datasets will be applied to assess the robustness of the findings.

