## Methods/design

This is a study protocol for a randomised controlled trial designed to test the effects of high intensity training compared to low intensity training on anxiety levels.

There will be a random 1:1 allocation into two groups. The two groups are high intensity exercise (1 × 4 minutes performed two times per week with a heart rate of 85–95% of maximal heart rate, corresponding to ≥ 16 on the 6–20 Borg scale) and low intensity exercise (45 minutes performed two times per week with a heart rate of approximately 60% of maximal heart rate, corresponding to 9–11 on the 6–20 Borg scale) [26]. The high intensity group will perform a 10-minute warm-up prior to the high-intensity bout, and a 5-minute cooldown. Due to the low intensity in the low intensity group, a warm-up is not considered necessary.

The total amount of training sessions for both groups will be eight. The high intensity exercise group will serve as the intervention group, while the low intensity exercise group will serve as an active control group.

The trial will be conducted in accordance with the Standard Protocol Items: Recommendations for Interventional Trials statement (SPIRIT) [27].

The trial has been approved by the Data Protection Officer at the University Hospital of North Norway and the Regional Committee on Health Research Ethics (approval number 714458) and registered at ClinicalTrials.gov (Trial registration number NCT06881758).

Participants will provide written informed consent before allocation to the two intervention groups, and they will be randomised into a high-intensity training group and a low-intensity training group, following baseline measures.

Randomisation will be performed using counterbalanced block randomisation in a 1:1 ratio, stratified by sex, to ensure an equal distribution of males and females across the study groups. Block sizes of four–six participants will be used. This will allow for a balanced representation of both genders in each condition. Randomisation will be conducted using a computer-generated random number sequence via the website https://www.randomizer.org/.

Outcomes will be measured immediately after inclusion (baseline), right after the very last exercise session, four weeks after the last exercise session (primary endpoint) and three months after the termination of the intervention period (secondary endpoint) (Fig. 1).

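### Twelve per group gives about 76% power, not 80%, for the two-tailed t-test that the sample size section names

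*Protocol article*

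**What the plan says.** All of the following is in the protocol article, section Sample size calculation, unless noted.

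- **Effect:** "The expected post-treatment BAI scores are 14 for the high-intensity group and 22 for the low-intensity group". Both groups are assumed to start at 30.
- **Error rates, spread and result:** "With a significance level (alpha) of 0.05, SD of 7 and 80% power, the required sample size is 24".
- **Test:** "This means we need 12 participants per group to detect significant differences using a two-tailed" t-test.
- **Tool:** "We conducted a power calculation using https://clincalc.com/stats/samplesize.aspx". The formula behind the calculator is not given.
- **Attrition:** about 20% is expected, and "the final target sample size is 30 participants (15 per group), representing the minimum required for adequate power". The section adds that more participants may be included if recruitment allows.
- **Allocation** (Methods/design): "There will be a random 1:1 allocation into two groups".

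The Statistical analysis section plans change scores analysed by repeated-measures ANOVA, with linear mixed models for missing data. It names age and baseline HADS-D as covariates. It does not name baseline BAI.

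**The concern.** The section names a specific test and attaches a specific power to it. At 12 per group the t-test has 22 degrees of freedom, and a sample size built on normal quantiles is then noticeably too small. The result of 12.02 was also rounded down, so there is no margin to absorb the difference.

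The target of 30 was chosen to leave 24 participants after the expected attrition. If 24 do not give 80% power, a trial that runs exactly as planned has less power than it reports. A null result from 24 completers would then be read against a power that the design does not have, and calling 30 the minimum for adequate power would not follow from the section's own inputs.

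**Working it through.** **Inputs, all from the protocol.** Difference 22 − 14 = 8 BAI points; SD 7; standardised difference 8/7 = 1.14; two-sided alpha 0.05; target power 80%; 1:1 allocation; attrition 20%.

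**Step 1: reproduce the stated figure.** The normal approximation for two means is

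n per group = 2 × (z₀.₉₇₅ + z₀.₈₀)² × SD² / difference² = 2 × (1.960 + 0.842)² × 49/64 = 12.02.

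Ordinary rounding gives 12 per group, or 24 in total, as stated. Rounding up would give 13 per group, or 26. Under the same approximation, power at 12 per group is 79.9%. Inflation for attrition is 24/(1 − 0.20) = 30, also as stated. The protocol's figures are therefore reproduced by this route.

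**Step 2: power of the test that is named.** For a two-sample two-tailed t-test with n per group, the degrees of freedom are 2n − 2, the noncentrality is 8/(7 × √(2/n)), and power comes from the noncentral t distribution.

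At n = 12, df = 22, the critical value is 2.074 and the noncentrality is 8/(7 × √(2/12)) = 2.80. Power is 76.3%, which is 3.7 points below the stated 80%.

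| Per group | Total analysed | Power, t-test | Power, normal approximation |
|---|---|---|---|
| 12 | 24 | 76.3% | 79.9% |
| 13 | 26 | 79.8% | 83.0% |
| 14 | 28 | 82.9% | 85.6% |
| 15 | 30 | 85.6% | 87.9% |

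The first size to exceed 80% is 14 per group, or 28 analysed. At 20% attrition that is 28/0.80 = 35 randomised (36 for equal arms), against the stated 24 and 30.

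**Step 3: what 30 randomised deliver.**

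- 20% lost, 12 per group: 76.3%
- 13 per group retained: 79.8%
- nobody lost, 15 per group: 85.6%

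**Step 4: can the planned analysis be relied on to recover 80%?** The protocol gives no baseline-to-follow-up correlation r, so the values below are assumptions. SD 7 is assumed at both times, with 12 per group.

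- *Change scores, as planned.* SD of change = 7 × √(2(1 − r)). At r = 0.3 this is 8.28 and power is about 62%. At r = 0.5 it is 7.00 and power is 76%. At r = 0.6 it is 6.26 and power is about 85%.
- *Adjustment for baseline BAI, not named in the plan.* Residual SD = 7 × √(1 − r²). At r = 0.3 this is 6.68 and power is about 80%. At r = 0.5 it is 6.06 and power is about 87%.

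The planned analysis can thus have less or more power than the simple t-test. Which it is depends on a correlation that is not stated.

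**The case against.** **This is an approximation, not a miscalculation.** That stands. The normal formula is widely used, it reproduces 24, and the inflation to 30 is exact. A reader might infer an arithmetic slip, and the document does not support that. But the section claims 80% for a t-test, and for that test the claim is wrong whichever formula produced it.

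**A gap of 3.7 points is small beside the uncertainty in the inputs.** Also fair. If the assumed difference were 8.4 instead of 8.0 points, 12 per group would give 80%. This limits the importance of the point but does not make the stated figure correct.

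**Thirty will be randomised, and more may be.** A reader might infer that 30 cannot deliver 80%. That goes too far. With no attrition, 30 give 85.6%, and the protocol allows further recruitment. Mixed models also use partial data from participants who drop out late, so treating the analysis as exactly 24 completers is a simplification. Still, 30 was derived so as to leave 24, and at 24 the power is 76.3%.

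**Covariate adjustment will make up the difference.** The document does not show this. It plans change scores with age and baseline HADS-D as covariates, omits baseline BAI, and states no correlation.

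**The SD may be too small, so true power could be much lower.** A reader might go on to compute power at larger SDs. The section says the calculation was informed by a previous study, though it does not tie the SD of 7 to that study specifically. Nothing in the document points to another value, so that extension has no basis here.

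**Conclusion.** The stated power is wrong as written, by a modest amount. On the protocol's own inputs, 12 per group gives 76.3% power for the two-tailed t-test it names, and the requirement is understated by 2 per group (14 instead of 12). With 30 randomised, power runs from about 76% at the expected 20% attrition to about 86% with none, so describing 30 as the minimum for adequate power is mildly optimistic.

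These figures assume a true difference of 8 points, a common SD of 7, equal groups, and an unadjusted comparison of post-treatment scores, which is what the sample size section describes. They are not the power of the change-score analysis that is planned; the document gives too little to compute that. Neither the design nor the conduct of the trial is put in question.

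**What to change.** In Sample size calculation, state that 24 completers give about 76% power for a two-tailed t-test, and about 86% if all 30 are retained. Delete the phrase that calls 30 the minimum required for adequate power.

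The cost is one or two sentences and a slightly less favourable figure. Enrolment, procedures and analysis need not change.

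Do not defend 80% by pointing to a baseline-adjusted analysis unless two things are done: baseline BAI is added as a covariate in Statistical analysis, and the assumed baseline-to-follow-up correlation is stated in the sample size section.

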### Recruitment

The participants will be recruited from two sources: from a waiting list at the Outpatient Clinic and by direct contact.

Patients aged 18–70 that are referred for anxiety disorders and who are currently on the waiting list for care at the Adult Psychiatric Outpatient Clinic at the Division of Substance Use and Mental Health will be one source of recruitment. The waiting list is long, and participation in the project will represent a great advantage for participants while waiting to receive treatment at the Hospital’s Outpatient Clinic. A secretary will distribute invitational letters. Participation in the project will have no impact on the participants’ waiting list status. Patients that have had their referral to the outpatient clinic rejected, but who fulfil the study’s inclusion criteria, will also be invited to participate.

Active recruitment via media is an additional strategy to recruit people suffering from anxiety. This recruitment strategy may reduce selection bias, in the sense that we will be able to include people who are not currently receiving treatment for anxiety by their general practitioners. The study has been presented in news stories online and in print media, and people with anxiety disorders (diagnosed or non-diagnosed) may contact the study organisers directly by phone or e-mail to discuss their participation.

Information about the study and screening for eligibility after verbal consent is carried out by phone. If the screening criteria are met and the person is interested in participating in the study, an appointment is scheduled. Potential participants will receive the participant information orally and in writing.

Prior to participation, a screening will be performed in order to examine whether potential participants fulfil the inclusion criteria and that the exclusion criteria are not met. The screening will include a clinical interview with a medical doctor, where the MINI-instrument will be used. A medical doctor will take the participant’s medical history, including but not limited to the elements of past history, natural functions and current medication.

Furthermore, a general medical examination including a clinical assessment of the cardiovascular, pulmonary, musculoskeletal and neurological systems will be performed by a medical doctor in order to ensure the patient can partake in the physical training safely. The study nurse will carry out the measurement of blood pressure, pulse, respiratory frequency, temperature, weight and height and waist circumference. A resting state EKG will be taken by the study nurse and assessed by a medical doctor. The following blood tests will be taken: haemoglobin and haematocrit, HbA1c, electrolytes, liver function tests, kidney function tests, TSH and fT4, lipids and PRO-BNP.

A medical doctor will, following the completion of examinations outlined above and the results of the tests, make an assessment regarding inclusion or exclusion in the study. Patients that are excluded for medical reasons will be followed up by the doctor and/or referred to another medical doctor for follow-up.

### Blinding

The study is not double-blinded, as this is not possible with the current intervention. However, the study nurse is blinded to the condition (high-intensity vs low-intensity), while the exercise physiologist is blinded to the scores on the outcome measures. Therefore, the study nurse does not know which condition the participants belong to, while the exercise physiologist has no insight into how the patients score on the various outcome measures.

### Participant adherence to the intervention, adverse events and concomitant care

The exercise physiologist will make appointments with the participants to perform the training interventions, and he will support adherence by following up on the participants, monitoring any adverse effects and providing real-time feedback.

Serious adverse events will be reported to the North Norway Regional Ethics Committee in accordance with the Health Research Act. Physical exercise is generally considered safe [34]; hence, no adverse events are expected; however, possible harms (e.g. injuries or severe events) are monitored using baseline values to oversee the condition of all participants during the trial.

Although the intervention is considered low risk, all participants will be continuously monitored for potential adverse events during each training session. The exercise physiologist and study nurse will record and report any untoward medical occurrences (e.g. cardiovascular symptoms, injuries, or other health-related complications).

In the event of any serious somatic or medical incident, the participant will immediately be withdrawn from the study and receive appropriate medical evaluation and treatment. The trial will be temporarily suspended or stopped if such events indicate that continued participation poses a health risk to any participant.

Serious adverse events will be reported to the Regional Committee for Medical and Health Research Ethics (REK North) and the Data Protection Officer in accordance with the Norwegian Health Research Act.

Given the short duration and low-risk nature of the intervention, no formal interim analyses or statistical stopping rules have been defined. The intervention is considered a low-risk and natural physical activity, similar to standard exercise routines recommended for the general population. Therefore, the likelihood of any serious adverse medical event is regarded as minimal.

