## Study setting

The study will take place at the Division of Substance Use and Mental Health at the University Hospital of North Norway, UNN-Åsgård, [name], Norway.

The study participants will be examined by medical staff (doctors) to assess eligibility for participation in the study. The screening will include a clinical interview where the MINI-interview will be used [28]. The following descriptive characteristics will be collected: sex, age, body weight, height, waist circumference, blood pressure, pulse, respiratory frequency, temperature, somatic and psychiatric diagnoses and current medication.

Furthermore, a medical examination will be performed in order to ensure the patient can handle the physical training. In addition, a resting state EKG will be taken, a blood sample will be drawn, and the following analyses will be performed: haemoglobin, haematocrit, HbA1c, electrolytes, liver function tests, kidney function tests, TSH and fT4, lipids and PRO-BNP.

Following inclusion in the study, a study nurse will assist the participants in performing the psychometric tests.

At the study Hospital, there are two separate rooms for physical training, fitted with treadmills and other equipment for physical training. The interventions (physical training) will be carried out with the supervision of an exercise physiologist.

The treadmills are of the type Lexco T560 (Lexco, South Korea) and the patients will also be fitted with heart monitor belts of the type Polar H10 (Polar Electro, Finland).

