## Discussion

Prior studies have found that physical exercise is beneficial for patients suffering from different types of psychiatric illnesses. Exercise may of course improve physical health but can also contribute to a reduction in psychiatric symptoms.

While prior studies have suggested that high-intensity training can lead to a reduction in anxiety, there is less evidence relating to the benefits of this type of intervention within the frame of mental health services.

Moreover, little is known about how high intensity training compares to low intensity training with respect to effects on anxiety levels in patients suffering primarily from anxiety disorders.

This is, to our knowledge, one of the first studies that compares these two different types of physical training for patients suffering from anxiety disorders.

Participants will be recruited by contacting those referred to the Study Hospital for outpatient treatment of anxiety and also by direct active recruitment through media.

Participants will undergo a thorough psychiatric and somatic examination to assess eligibility and to exclude those who may be physically unfit to participate. We will randomise the participants into a high-intensity training group and a low-intensity training group, in order to study whether the intensity of training is of importance to outcome in terms of reduced anxiety symptoms.

The duration (four-week intervention) was chosen based on feasibility within the clinical setting, but also previous evidence that high-intensity interval training (HIIT) can yield measurable psychological and physiological benefits within short timeframes [21]. This supports a short, structured and time-efficient design suitable for clinical practice.

Complete blinding is not feasible or possible in exercise interventions, as participants and trainers are aware of the training intensity. To minimise bias, however, the outcome assessor (study nurse) will be blinded to group allocation, and the exercise physiologist will not have access to any outcome data.

This study will add to the present-day understanding of the efficacy of physical training for people suffering from anxiety, and for the importance of physical training for mental health in general.

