## Data statement section

Data (including diagnostics, psychometrics, results from blood tests and training data) for each participant will be securely stored in the Electronic Health Records at the Study Hospital. Source documents, including dates and participant IDs, will be scanned and saved as electronic copies, and the paper material will be destroyed.

In the data-analysis process, each participant will be given a unique ID code and the corresponding ID will be kept separate in a secure location.

Data will be stored for five years after the termination of the trial after which the data will be anonymised.

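### The blinded outcome assessor also shares in recording adverse events from training, so assessor blinding is at risk and the sections need reconciling

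*Protocol article*

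**What the plan says.** Three sections of the protocol article bear on this.

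- **Blinding.** The article states that "the study nurse is blinded to the condition (high-intensity vs low-intensity), while the exercise physiologist is blinded to the scores on the outcome measures". It then repeats as fact that the nurse does not know which arm a participant is in.
- **Discussion.** After conceding that participants and trainers cannot be blinded, the article offers a measure against bias: "the outcome assessor (study nurse) will be blinded to group allocation".
- **Participant adherence to the intervention, adverse events and concomitant care.** The third paragraph says that "all participants will be continuously monitored for potential adverse events during each training session". The next sentence assigns the duty to two people: "The exercise physiologist and study nurse will record and report any untoward medical occurrences".

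The nurse's contact with the outcomes is described elsewhere. Under Study setting, "a study nurse will assist the participants in performing the psychometric tests". Under Recruitment, the nurse measures blood pressure and takes the resting EKG at screening. Under Methods/design and in Table 1, BAI, HADS, blood pressure and EKG are all repeated after the intervention, the first time immediately following the final session.

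**The concern.** Assessor blinding is the only protection against assessment bias that the article claims on the outcome side. It holds only if the nurse does not learn what kind of session a participant has done. A joint duty to record untoward events, placed directly after a sentence about in-session monitoring, reads naturally as including events that arise in sessions. An event report with ordinary context (when in the session, at what effort, after how many minutes) would tend to give the arm away.

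Blood pressure is at stake first. It is a secondary outcome with a directional hypothesis in favour of high intensity, and it is measured by staff. The EKG recording, from which heart rate variability is derived, is also taken by staff. The nurse also helps participants with the questionnaires, so knowledge of the arm could affect prompting or clarification there. Finally, if the blinding statement is carried into the results paper without qualification, readers may credit the trial with more protection than its own assignment of duties supports.

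**Working it through.** The article gives no figure on this point to reproduce, so the check sets the sections side by side.

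**Step 1. Can the arms be told apart?** Inputs are from Methods/design.

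| | High intensity | Low intensity |
|---|---|---|
| Warm-up | 10 min | none |
| Main bout | 4 min at 85–95% of maximal heart rate | 45 min at about 60% |
| Cooldown | 5 min | none stated |
| Borg rating (6–20) | 16 or more | 9–11 |
| Total | 10 + 4 + 5 = 19 min | 45 min |

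The sessions differ by 45 − 19 = 26 minutes, and the Borg ranges do not overlap. Only 4 of the 19 minutes (4/19 = 21%) are at the high heart rate, so it would be wrong to describe the whole session as high intensity. Duration, structure and peak effort still separate the arms for anyone present, or for anyone told the circumstances of an event.

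**Step 2. Does the nurse's duty reach session events?** The adverse-events section first gives the exercise physiologist the monitoring of adverse effects. Two paragraphs later it describes continuous monitoring in each session, then names physiologist and nurse together as recorders. The recording sentence sets no boundary between events in sessions and events reported elsewhere. On its natural reading the nurse handles both.

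**Step 3. Is there a safeguard?** Neither the Blinding section nor the Discussion says how the nurse stays blinded while recording events. The adverse-events section does not mention blinding at all.

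**Step 4. Which outcomes could be affected?**

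- *Blood pressure and EKG recording.* Taken by the nurse at screening. That the nurse also takes them at follow-up is an inference from the Discussion's description of the nurse as outcome assessor; no section assigns it directly.
- *BAI and HADS.* Self-report, completed by participants who know their training intensity. Nurse blinding can limit only the influence of the person assisting. It cannot remove the participants' own expectations.

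**Step 5. What does the text not establish?** Sessions are described under Study setting as follows: "The interventions (physical training) will be carried out with the supervision of an exercise physiologist". The nurse is not named there, and no section says that the nurse attends sessions or sees heart-rate or treadmill data.

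**The case against.** The strongest reply is that the text is compatible with intact blinding. No section puts the nurse in the training room. The recording sentence covers health complications in general and can be read as the physiologist recording what happens in sessions and the nurse recording what participants mention at visits. The article is also open about its limits: it calls both scales self-report, says the study is not double-blinded, and says that participants know their training intensity.

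Much of this stands, and it rules out several stronger readings that a reader might infer:

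- *That the blinding fails, with exposure at each of the 8 sessions.* This would need the nurse to be present at sessions or told about them in detail. Neither is stated.
- *That assessment immediately following the final session reveals the arm.* It is plausible that the nurse does this assessment, but it is not stated. Both arms arrive from exercise, and the high-intensity arm has had a cooldown.
- *That shared records unblind both staff members.* The Data statement section says: "Data (including diagnostics, psychometrics, results from blood tests and training data) for each participant will be securely stored in the Electronic Health Records". That is a storage location; it says nothing about who may open which data.
- *That the article hides the self-rating of its primary outcomes by unblinded participants.* It discloses this.

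What the reply does not remove is the conflict itself. The blinding claim is unqualified, the shared duty follows directly on in-session monitoring, and nothing reconciles the two. The benign reading has to be supplied by the reader.

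**Conclusion.** The point holds as a risk to assessor blinding and as an inconsistency between sections that should be corrected. It does not hold as a demonstration that the nurse is unblinded.

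The size of any resulting bias cannot be estimated from the document, because neither the frequency of session events nor the content of the reports is known. The risk falls chiefly on blood pressure and the EKG recording, and to a lesser degree on the nurse-assisted BAI and HADS. The primary analysis is not invalidated.

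The conclusion rests on two assumptions: that the shared recording duty includes events arising in sessions, which is the natural reading, and that the nurse carries out the follow-up assessments, which the Discussion implies. If the sponsor confirms that the nurse records only events reported at assessment visits, without training details, what remains is a matter of wording.

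**What to change.** Reconcile the adverse-events section with the Blinding section and the Discussion:

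1. State that the exercise physiologist, who is unblinded and already monitors adverse effects, records events arising in training sessions.
2. Limit the nurse to events that participants report at assessment visits, elicited without disclosure of training details.
3. Log any occasion on which the nurse learns the allocation, with the date, so that it can be reported with the results.
4. Where the Discussion offers assessor blinding as protection against bias, add that it does not remove bias from BAI and HADS, which are self-rated by participants who know their training intensity.

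This needs no extra staff. The downside is that one person instead of two records in-session events. Recruitment was expected to finish in March 2026, so the first three changes may reach only some participants and follow-up visits. If they count as a substantial change to study procedures, they need ethics committee approval first, as the Ethics and dissemination section provides. The fourth can be made in any case before results are reported, together with a plain account of how events were in fact recorded.
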